## Abstract

**Background:**

Coronary heart disease and depression are both common health problems and by 2020 will be the two leading causes of disability worldwide. Depression has been found to be more common in patients with coronary heart disease but the nature of this relationship is uncertain. In the United Kingdom general practitioners are now being remunerated for case-finding for depression in patients with coronary heart disease, however it is unclear how general practitioners should manage these patients. We aim to explore the relationship between coronary heart disease and depression in a primary care population and to develop an intervention for patients with coronary heart disease and depression.

**Methods/design:**

This programme of research will consist of 4 inter-related studies. A 4 year prospective cohort study of primary care patients with coronary heart disease will be conducted to explore the relationship between coronary heart disease and depression. Within this, a nested case-control biological study will investigate genetic and blood-biomarkers as predictors of depression in this sample. Two qualitative studies, one of patients' perspectives of treatments for coronary heart disease and co-morbid depression and one of primary care professionals' views on the management of patients with coronary heart disease and depression will inform the development of an intervention for this patient group. A feasibility study for a randomised controlled trial will then be conducted.

**Discussion:**

This study will provide information on the relationship between coronary heart disease and depression that will allow health services to determine the efficiency of case-finding for depression in this patient group. The results of the cohort study will also provide information on risk factors for depression. The study will provide evidence on the efficacy and feasibility of a joint patient and professional led intervention and data necessary to plan a definitive randomised controlled trial of the intervention.

## Background

The World Bank and World Health Organisation have predicted that by 2020, coronary heart disease (CHD) and depression will be the two top causes of global health burden and disability[1]. As well as causing personal suffering, depression is a major public health problem responsible for 100 million lost working days in England and Wales at a cost of £9 billion per annum [2].

In the United Kingdom (UK), depression is one of the commonest reasons for consulting a general practitioner (GP). Up to 17% of consecutive GP attendees suffer from depression [3]. In the UK, 95% of people suffering from depression are treated solely in primary care [4].

Depression has been found to be more common in patients with coronary heart disease (CHD) with a prevalence of 20% [5]. Depression also increases the incidence and recurrence of acute coronary syndromes and death in patients with heart disease [5]. This increase in cardiac risk is independent of other risk factors for CHD [5]. The reason for the increased morbidity and mortality is unclear but may be due to increased activity of the immune/inflammatory pathways in depression, activating atherogenesis and plaque formation [6].

Depression is associated with a 50% increase in the costs of long term medical care after controlling for the severity of the physical illness[7]. Some of these costs are related to the association between depression and adverse health risk behaviours such as smoking, diet, lack of exercise and a lack of adherence to self-care regimes. Depression as cause or consequence of physical illnesses such as CHD may exacerbate the perceived severity of symptoms and with an increase in health service utilisation[7]. Treating depression and improving outcomes for depression has been shown to reduce health costs in people with physical illness[7,8]. It therefore seems important to address the care of patients with coronary heart disease and co-morbid depression in the primary care setting.

In the UK, GPs are now remunerated for depression case-finding in patients with CHD [9]. This is because evidence from two large trials in the United States has provided an indication in *post hoc *sub-group analyses that there may be cardiovascular benefits from treating depression using antidepressant medication[10,11]. Mortality seems to have been reduced in those whose depression improved and in those who took sertraline [12,13]. However, the natural history, morbidity and mortality of depression in the primary care population of patients with CHD are not known. It is also unclear how primary care professionals should manage additional cases of depression that may be identified in their CHD patients. Observational cohort studies are needed to help determine the effect of policy implementation on the patient's cardiac and depression outcomes as well as the effects of co-morbidity on morbidity and mortality. If the incidence of depression in patients with CHD is not solely a function of the current physical status, a cohort study will enable other factors associated with the incidence of depression e.g. factors relating to quality of life, illness attribution and social support, to be determined.

There are a number of treatment options for managing depression in primary care e.g. antidepressant medication, supervised exercise, guided self help, problem solving, computerised cognitive behavioural therapy (cCBT), group or individual CBT or interpersonal therapy (IPT) [4]. However the treatment preferences of patients with CHD are unknown. Primary care professional treatment preferences for managing depression in this population are also unknown. As with most physical illness in primary care settings, it is also unclear where the boundary exists between distress secondary to the physical condition and depression that would benefit from treatment. Qualitative studies with patients and their primary care professionals are needed to explore this further. A recent working party on the management of depression in CHD concluded that randomised controlled trials of stepped depression care versus treatment as usual for patients with CHD and depression are needed [5]. This programme of research will inform a randomised controlled trial of the effectiveness and cost-effectiveness of a case management approach to manage primary care patients with coronary heart disease and co-morbid depression. Case management has been shown to improve outcomes for depression in primary health-care settings [14], but there has been no research to determine whether it is effective in patients with symptomatic coronary heart disease. Case management has been defined as 'taking responsibility for following-up patients; determining whether patients were continuing the prescribed treatment as intended; assessing whether depressive symptoms were improving; taking action when patients were not adhering to guideline based treatment or were not showing expected improvement'[15]. It consists of five essential components [14]:

1. identification of patients in need of services

2. Assessing individual patient's needs

3. Developing a treatment plan

4. Coordination of care

5. Monitoring outcomes and altering care when favourable outcomes are not achieved

A randomised controlled trial is necessary to determine whether case management for this population is more effective than treatment as usual both in terms of depression and cardiac outcomes. A pilot randomised controlled trial is needed first to inform the design of the definitive randomised control trial.

This protocol describes a programme of research to develop and test a stepped care intervention for depression and coronary heart disease in primary care. It consists of 4 inter-related studies.

1. A 4 year cohort study of patients with coronary heart disease

2. A qualitative study of patients with coronary heart disease and co-morbid depression treatment preferences

3. A qualitative study of general practitioners (GPs) and practice nurses (PNs) treatment preferences for this patient group

4. A pilot randomised controlled trial of a case management programme for depressed primary care patients with CHD.

The first three studies will inform the development of the pilot randomised controlled trial (study 4). As the four studies are closely related and the randomised controlled trial depends on the conduct and findings of the other studies, the study protocols will be described in turn.

## Study 1: Cohort Study

### Objectives

The objectives of the cohort study are to:

• Determine prevalence, incidence rate and risk factors of depression in primary care patients with CHD

• Explore and describe the course, relationship, prognosis and current management of physical and depressive symptoms in primary care patients with CHD and co-morbid depression over a four-year period.

• To determine the effect of co-morbid depression on mortality, symptom severity, quality of life, disability, pain, service use (at all levels) and service costs, and lost employment costs in primary care patients with CHD.

•In a subsample, to investigate genetic variation and blood biomarkers that characterise depression in this cohort.

### Hypotheses

In addition to the estimation of prevalence and incidence of depression among patients with CHD, the main hypotheses to be tested in this study are:

• That symptoms and disability caused by CHD are associated with depression and that in patients with symptomatic CHD, the severity of symptoms of CHD, is a greater predictor of developing a depressive episode than a past history of depression.

• That in patients with symptomatic CHD, the severity of depressive symptoms as measured by the Hospital Anxiety and Depression Scale (HADS) [16] is related to the severity of CHD symptoms as measured by the Rose Angina Questionnaire [17] and SF-36[18].

• That patients with CHD and depression use more services for the management of their CHD, are more costly, and have higher lost employment costs than non-depressed primary care patients with CHD.

#### Methods/design

This is a naturalistic cohort study in primary care in South London, United Kingdom. Eligible consenting patients will be assessed at baseline and then at 6 monthly intervals for up to 4-years.

#### Study Population

Patients with CHD will be recruited from practice CHD registers. Two subgroups will be identified:

1. Patients with CHD and a current diagnosis of depression

2. Patients with CHD who are not currently depressed

#### Recruitment of study population

GPs are remunerated for keeping CHD registers under the Quality and Outcomes Framework. Practices participating in this Framework and based in South London will be recruited by the Greater London Research Network (GLRN). All patients on the CHD registers in participating general practices will be invited to participate in the study. Consenting patients will be assessed at baseline and then every 6 months over a 4 year period.

#### Measures

Information on sociodemographic status, past medical and psychiatric history, prescribed medication and medication compliance will be collected. Measures used at baseline and follow-ups [17-31] are shown in Table 1.

**Table 1 T1:** Measures that will be used at baseline and follow-up assessments

Measure	Baseline	Follow-up
		

Modified Rose Angina Questionnaire [17]	x	x

Guy's Hospital Chest Pain Questionnaire [19]	x	x

Specific Activity Scale[20]	x	x

General Health Questionnaire-12 (GHQ-12_ [21]	x	

Hospital Anxiety and Depression Scale (HADS)[22]	x	x

Clinical Interview Schedule-Revised (CIS-R) [23]	x	

Patient Health Questionnaire-9 (PGQ-9) [24]	x	x

EuroQoL (EQ-5D) [25]	x	x

Medical Outcomes Survey Short Form-12 (SF-12) [18]	x	x

List of Threatening Experiences Questionnaire [26]	x	x

Social Problems Questionnaire (SPQ) [27]	x	x

Client Service Receipt Inventory (CSRI) [28]	x	x

Brief Illness Perceptions Questionnaire (B-IPQ) [29]	x	x

Psychological Outcome Profiles Questionnaire (PSYCHLOPS) [30]	x	x

Rapid Estimate of Adult Literacy in Medicine (REALM) [31]	x	

In addition, for the nested biological study we will investigate "at risk" genetic polymorphisms in neurotransmitters and immune genes (for example, serotonin transport or interleukin-6) and inflammatory biomarkers (for example, C-reactive protein and cortisol).

#### Inclusion criteria

• Currently registered with GP

• On the coronary heart disease register of participating general practitioners

• Over 18 years of age

#### Exclusion criterion

• Patients only temporarily registered with participating practices

#### Sample size calculation

The national prevalence of CHD in primary care as estimated by the Quality and Outcomes Framework (QOF) disease registers is 3.5%. We estimate that in patients with CHD, 20% will have a diagnosis of depression.

In a practice population of 10,000 people, we would therefore expect 350 patients with CHD of which 70 would be currently be depressed. Three practices with an average population of 10,000 patients will be recruited initially. Allowing for 80% participation, this will provide ~ 670 patients with CHD but no depression and ~168 patients with CHD and co-morbid depression. A cohort of this size would be large enough to estimate rates to acceptable limits on the basis of the above figures. The total sample size (~800) would produce up to 4800 data points over 4 years of follow-up at 6-monthly intervals (6 measures per person). This total sample size will be effectively somewhat smaller, firstly because of attrition and secondly because of the lack of independence of the repeated measures. Assuming an intra-person correlation of 0.2, the sample size would reduce by approximately 1/3 and if 20% dropout is also assumed, a total sample size of ~3130 data points would be collected, large enough to allow modelling of the associations between physical and mental illness as specified in the hypotheses.

#### Analysis

A descriptive analysis of prevalence and incidence, course, prognosis and management of physical and depressive symptoms will be undertaken. Risk and rate ratios will be estimated for the effect of depression on: symptom severity, quality of life, functional status, pain, and service use. An economic evaluation will be conducted to establish economic burden. Multiple regression using methods for repeated measures will be used to explore the relationship between depression, CHD and other possible confounding factors using the longitudinal data. The time course will be examined by including time as a main effect and as an interaction with the physical illness. The relationship of depression severity to outcome measures will also be explored using multiple regression analyses.

Service costs will be calculated by combining service use data from the Client Service Receipt Inventory with appropriate unit cost information. Lost employment costs will be estimated by multiplying lost workdays by daily wage rates. Regression models will be used to identify patient characteristics that explain variations in costs. Due to the expected skewed distribution of the cost data we will use bootstrapping and generalised linear models. It would be expected that service inputs over time (represented by service costs) would influence clinical measures and quality of life. To assess this we will also use regression models with symptoms and quality of life as dependent variables and the costs of specific services entered as independent variables, along with socio-demographic covariates.

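### The Study 1 model of service costs on symptoms and quality of life names only socio-demographic covariates, so confounding by prior severity biases it toward harm and can reverse the sign of a true benefit

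*Protocol article*

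**What the plan says.** All of this is in the protocol article, Study 1.

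- **Aim of the model (Analysis).** The expectation is directional: "It would be expected that service inputs over time (represented by service costs) would influence clinical measures and quality of life".
- **Model (Analysis).** To assess that expectation, the plan takes "symptoms and quality of life as dependent variables and the costs of specific services entered as independent variables, along with socio-demographic covariates". Outcome, exposure and adjustment set are all named. No lag between costs and outcomes is given, and no earlier outcome score.
- **Morbidity as a source of service use.** The third hypothesis is that "patients with CHD and depression use more services for the management of their CHD, are more costly". The Analysis section plans the following: "Risk and rate ratios will be estimated for the effect of depression on: symptom severity, quality of life, functional status, pain, and service use". It also says: "Regression models will be used to identify patient characteristics that explain variations in costs". The article's Background says of depression accompanying physical illness that it "may exacerbate the perceived severity of symptoms and with an increase in health service utilisation".
- **Design and data.** The cohort is naturalistic and assessed every 6 months. Table 1 lists HADS, PHQ-9, the modified Rose Angina Questionnaire, SF-12, EQ-5D and the service receipt inventory (CSRI) at both baseline and follow-up.

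**The concern.** Services are not allocated at random in this cohort; patients who are more unwell can be expected to receive more of them. The protocol builds on that idea when it treats service use as a consequence of depression. In this one model it turns the direction round, making morbidity the outcome and cost the exposure, without holding earlier morbidity fixed. Socio-demographic variables cannot stand in for it. This is confounding by indication: cost partly acts as a marker of how ill the patient already was.

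At stake is the reading of the coefficient. A service that helps may look weaker than it is, or useless, or harmful. That would mislead in a programme intended to improve the management of these patients, all the more because the aim is worded as influence.

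**Working it through.** The documents attach no sample size, power or effect size to this model, so there is no stated figure to reproduce. The check is of the direction of the bias and of the conditions under which the sign reverses.

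**1. Does other wording supply the missing covariates?** The Analysis section mentions a model to "explore the relationship between depression, CHD and other possible confounding factors using the longitudinal data". That is the repeated-measures model of depression and CHD. The cost model comes in the next paragraph with its own covariates, so the phrase does not extend to it.

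**2. Formula.** Let S be prior severity, C service cost and Y later symptoms (higher = worse), with S and C in SD units:

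- C = c·S + noise
- Y = b·S + t·C + noise, where t is the true effect of cost (negative = benefit)

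Leaving S out, the slope on C is t + b·c. If b and c are positive, the bias b·c is positive, that is, toward harm. For quality of life, where higher is better, the signs flip but the direction is still toward harm.

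**3. Illustration.** All values of b, c and t are assumptions. With t = -0.10:

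| b | c | Bias b·c | Slope t + b·c |
|---|---|---|---|
| 0.5 | 0.3 | +0.15 | +0.05 |
| 0.6 | 0.5 | +0.30 | +0.20 |
| 0.7 | 0.6 | +0.42 | +0.32 |

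**4. When does the sign reverse?** Only when b·c is larger than the true benefit. With b = 0.6, c must exceed 0.10/0.6 = 0.17 for a benefit of 0.10, 0.20/0.6 = 0.33 for 0.20, and 0.30/0.6 = 0.50 for 0.30.

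**5. Simulation.** Ordinary least squares, N = 800 (the article's approximate cohort size), 300 replicates per cell, b = 0.6, with one socio-demographic variable in every model. Cells show the mean estimate without prior severity, and the share of replicates with the wrong sign:

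| True effect | c = 0 | c = 0.1 | c = 0.2 | c = 0.3 | c = 0.5 |
|---|---|---|---|---|---|
| -0.1 | -0.10 (0%) | -0.04 (11%) | +0.01 (65%) | +0.08 (99.7%) | +0.20 (100%) |
| -0.2 | -0.20 (0%) | -0.15 (0%) | -0.09 (0.7%) | -0.02 (27%) | +0.10 (100%) |
| -0.3 | -0.30 (0%) | -0.24 (0%) | -0.18 (0%) | -0.12 (0%) | 0.00 (51%) |

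With no severity-cost link there is no bias. With any positive link the estimate moves toward harm. Adding prior severity brought every mean to within 0.005 of the true value, with no wrong signs. That recovery holds by construction, because prior severity is the only omitted confounder simulated.

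**The case against.** **The article is a condensation.** The sentence sketches an additional model and does not say that socio-demographics are the sole adjustment; an analysis plan not shown could add more. That is fair as far as it goes. But the article does state an adjustment set for this model, and the point concerns the set stated, not a silence.

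**The hypothesis is narrower than severity driving the cost of every service.** It compares depressed with non-depressed patients, and the costs model speaks of patient characteristics without naming severity. This stands: the severity-cost link is an inference, though the Background and the listing of service use as an effect of depression both support it. Its strength is unknown.

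**Two stronger readings are tempting and are not supported.**

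- A reader might infer that the model will show harm however large the true benefit. The formula says otherwise: with t = -0.3, b = 0.6 and c = 0.3 the slope is -0.3 + 0.18 = -0.12, an attenuated benefit with the right sign.
- A reader might infer that reverse causation is certain because cost and outcome come from the same wave. The documents do not give the timing, and the reference to inputs over time may mean accumulated use. Reverse causation is added only if costs and outcomes are taken over the same period. Confounding by prior severity does not depend on that.

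**The analysis is secondary.** It matches no listed cohort objective or main hypothesis, and the Background reserves the effectiveness of case management for a randomised trial. This limits the consequence but does not make the stated model sound.

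**Conclusion.** The concern holds as a bias toward harm. With the named covariates alone, a true benefit of services will be attenuated if prior severity raises both cost and later symptoms. Its sign can reverse if the severity-cost link is strong relative to the benefit. Under the assumed ranges the bias is +0.15 to +0.42 SD. That is enough to reverse a benefit of 0.10 throughout, but not always one of 0.20 or 0.30. The direction rests on a link that the protocol itself expects; the size rests wholly on assumed values.

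The change is worth making because the better model uses data already collected. The consequence is confined to a secondary observational analysis in Study 1; nothing here affects the pilot RCT in Study 4.

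**What to change.** Replace the stated model with a lagged one. Regress symptoms and quality of life at wave t on service costs over the interval from t-1 to t. Adjust for the same symptom and quality-of-life scores, depression status and CHD severity at wave t-1, together with socio-demographics. Table 1 supplies these at every wave: HADS and PHQ-9 for depression, the Rose Angina Questionnaire for CHD symptoms, and SF-12 and EQ-5D for quality of life. The CIS-R is listed at baseline only, so depression status at later waves would have to come from HADS or PHQ-9.

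State the timing of costs relative to outcomes, and report the result as an association rather than an influence. Deterioration between t-1 and t can still raise both cost and symptoms, so lagged adjustment reduces the confounding without removing it.

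**Cost.** A little more modelling, and one wave used as the lag. The Time Scale section expects at least 6 follow-ups after baseline, so a patient with complete data has 7 waves and still contributes 7 - 1 = 6 outcome waves. No new measures or visits are needed.
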